Kim and Kochanska [11] reported differential susceptibility to parenting with children’s temperament, or negative emotionality, as susceptibility marker. Infants with high negative emotionality developed the highest levels of effortful control and self-regulatory compliance toward their mothers in positive mother-child relationships, but the lowest levels in negative mother-child relationships. Mother-child relationship quality did not affect effortful control of self-regulation for children with low negative emotionality. Similar results were found for childcare quality as environmental factor and behavioral problems as outcome [12]; children with high negative emotionality were more affected by childcare quality, for better and for worse. Gene-by-environment interactions may also be involved in environmental effects on parenting. Parents with so called susceptibility genes were found to be less sensitive in the case of negative environments characterized by early childhood maltreatment, depression and/or daily (parenting) stressors, whereas they displayed the highest levels of sensitivity in positive, supportive environments [13, 14].

An important limitation of these studies is their correlational design. In correlational studies, the environment and the susceptibility marker may be correlated; children’s genetic make-up and their parenting environment may at least partly be caused by the same underlying factor, their parents’ genes [15]. Such gene-environment correlations make it impossible to examine the true moderating effect of heritable child characteristics in the relation between parenting environment and child outcomes. In the current study, we break the gene-environment correlation by using a randomized controlled trial with experimental manipulation of the parenting environment. Experimental manipulation is supposed to lead to positive changes in the family interactions and relationships, in particular in those parents and children who are more susceptible to the environment and profit more from the intervention whereas more susceptible individuals in control group families experiencing (mild) setbacks, conflicts or adversities may suffer more than their less susceptible counterparts.

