### Aims and hypotheses

1) The primary aim of the Leiden Consortium on Individual Development (L-CID) is to study the effect of the VIPP-Twins on parental sensitivity and sensitive discipline of the primary parent, one month after the intervention and two years after the intervention (see Fig. 1 for an overview of the different aims). It is expected that sensitivity and sensitive discipline of parents in the intervention condition will significantly increase post-intervention, compared to sensitivity and sensitive discipline of parents in the control condition, who have a similar number of (‘dummy’) contacts with the interveners. 2) The secondary aim is to examine the efficacy of the intervention in enhancing children’s levels of behavioral control and social competence, through increased parental sensitivity and sensitive discipline. 3) A tertiary aim is to test what works for whom by testing the differential susceptibility theory using temperamental reactivity and dopamine-related genotype as main susceptibility markers. We will examine whether the intervention effects on parental sensitivity and sensitive discipline are moderated by parents’ sensory sensitivity [24]) and genotype (dopamine related genetic pathways). 4) More exploratory, we will examine whether the intervention effect on children’s behavioral control and social competence is moderated by children’s genotype (dopamine related pathways) and/or by their reactive temperament, two markers of differential susceptibility that might overlap only partially and thus may have independent moderator effects. 5) Moreover, we aim to explore mediators of change in child outcomes by examining the intervention effect on changes in children’s neural activation and hormonal reactivity, and whether these differences mediate the observed changes in children’s behavioral outcomes.

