#### Randomization

Randomization to the VIPP-Twins or control condition is done at the family level in a ratio of 2:3, using a computer-generated blocked randomization sequence, with a block size of 19 families based on timing of the intervention and stratified by twin gender. Assignment of participants is performed by an independent researcher who is not involved in data collection or coding. Allocation will be performed after the second pretest, right before the start of the intervention, in order to prevent selective attrition. Researchers, interveners and participants are blinded to assignment before, but not after, randomization, because of the open-label design. To minimize bias based on knowledge about allocation of participants, coders and research assistants who carry out the post-intervention home-visits and laboratory sessions are blind to treatment allocation.

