### Sample size and power

A meta-analysis on the effects of VIPP-SD on caregiver sensitivity indicates a combined effect size of d = 0.47 [20]. For our primary aim, testing the effect of VIPP-Twins on parental sensitivity and sensitive discipline with a repeated measures analyses with α = .05 and a sample size of 225 families (including 450 children), the power is > 90 % (repeated measures ANOVA within-between interaction, G*Power 3.1.9.2). For our secondary aim (main effects on children’s social competence and behavioral control), the power of the multilevel analysis is > 90 %. For the third and fourth aims, testing moderator effects, the power is > 80 %. For the fifth aim, testing mediating mechanisms, the power is > 90 %.

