#### Third and fourth aim

##### Susceptibility markers

Our third and fourth aims are to test if the intervention effects on parenting or child outcomes are moderated by parental or children’s genotype or reactive temperament in line with a differential susceptibility model, [40]). Buccal cells will be collected from the children and both parents using Whatman Omniswabs in order to obtain information about genetic polymorphisms of specific dopamine related genes. Parental and children’s reactive temperament will be measured using subscales from Rothbarth’s temperament questionnaires (fearful and reactive temperament, sensory sensitivity; [34, 41]).

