To examine the moderation of the intervention effect, the third and fourth aim of our study, we will include an additional interaction term in the models of aims 1 and 2. For parenting outcomes, we will include the interaction between condition and parental susceptibility markers (genotype and reactive temperament). For child outcomes, we will include an interaction term between parenting and children’s susceptibility markers. For our final aim, exploring mechanisms of intervention effects, we will use the Preacher-Hayes approach [45] in a multilevel or repeated measures design to test for intervention effects on neurobiological variables and examine whether these variables mediate the observed changes in children’s behavioral control and social competence.

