### Strengths and limitations

An important strength of the study is that the intervention program VIPP-SD has a sound theoretical basis in attachment theory as well as coercion theory [19]. In addition, several previous randomized trials have found empirical evidence for the efficacy of the original version of the VIPP and for several adaptations of the program [20]. Therefore, we have a clear hypothesis about the efficacy of the program, and we can now fill in the gap that exists in knowledge of moderating and mediating factors in the program’s effectiveness.

The random assignment of families to the experimental or control condition is the most important strength of the study design. Random assignment of families to the experimental condition reduces potential gene-environment correlations, and opens the way to test the true moderating effect of participants’ characteristics on intervention efficacy. Because of the longitudinal design of the study with multiple follow-up measures, we can test both short-term and long-term effects of the intervention program. Intervention effects are not only measured on the behavioral level, but also on the hormonal and neural level. Information about intervention effects on neurobiological levels of functioning may explain the long lasting intervention behavioral effects that have previously been documented [10]. A final strength of the study concerns the observational and ambulatory measures, which reduce possible reporter bias related to self-report questionnaire studies.

The study has some limitations that should be noted. First, the large sample size demands multiple interveners, which may lead to divergences in program implementation. However, given the extensive training of interveners, the use of a standardized manual, and frequent supervision, we expect high treatment fidelity. A possible limitation in examining differential susceptibility to intervention effects and the mediators for change in child outcomes is the twin sample. Twin families may be different from families with singletons on several aspects, which may decrease the generalizability of the findings (but see: [46, 47]). The twin sample however also provides the opportunity to test for differential susceptibility within families and for genetic modelling of intervention effects.

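### Aim 4 moderation by child genotype is confounded by the trained parent's genotype if aims 2 and 3 both hold, and no planned model separates the two; at 225 families the inflation is modest

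*Protocol article*

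**What the plan says.** All references are to the protocol article.

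- **Aims and hypotheses.** Aim 2 expects child outcomes to improve through better parenting. Aim 3: "We will examine whether the intervention effects on parental sensitivity and sensitive discipline are moderated by parents’ sensory sensitivity" and by dopamine-related genotype. Aim 4, introduced as more exploratory, asks whether the intervention effect on child outcomes is moderated by the child's genotype or reactive temperament.
- **Intervention.** Only the primary parent attends the first four of the five sessions.
- **Statistical analyses.** For every aim the effect analysed is VIPP-Twins against control, by intention to treat. For moderation, "we will include an additional interaction term in the models of aims 1 and 2": condition × parental markers for parenting outcomes, and parenting (not condition) × child markers for child outcomes. No parental marker enters a child-outcome model.
- **Differential intervention effects.** After naming parents' genes as the possible common cause that weakens correlational studies, the article states: "In the current study, we break the gene-environment correlation by using a randomized controlled trial with experimental manipulation of the parenting environment".
- **Strengths and limitations.** Random assignment "opens the way to test the true moderating effect of participants’ characteristics on intervention efficacy".
- **Susceptibility markers.** "Buccal cells will be collected from the children and both parents", so the parental genotype will be available.

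**The concern.** Randomisation makes condition independent of every genotype. It does not make the child's genotype independent of the parent's, and it does not make the change in parenting that the programme produces independent of the parent's genotype. The programme acts through the parent. If carrier parents change more, their children are exposed to a larger change, and those children are themselves more often carriers. The randomised effect on the child then differs by child genotype although no child is more susceptible than another.

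This is a form of the shared-parental-gene problem that the Background says the design overcomes. As the models stand, a positive aim 4 result under the condition-based definition would not distinguish child susceptibility from parental susceptibility passed on through parenting. That matters because the Abstract and the concluding paragraph present the trial as an experimental test of differential susceptibility.

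**Working it through.** **1. The plan's own figure.** Inputs: "α = .05 and a sample size of 225 families (including 450 children), the power is > 90"%; the meta-analysis "indicates a combined effect size of d = 0.47" on caregiver sensitivity; allocation "done at the family level in a ratio of 2:3", so 225 × 0.4 = 90 treated and 135 control families. For a two-sided post-test comparison, SE = √(1/90 + 1/135) = 0.136, and 0.47/0.136 − 1.96 = 1.49, giving power of 93.2%. The stated figure for the primary aim reproduces. The figure of more than 80% for moderation cannot be checked, because no effect size, marker frequency or correlation is given.

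**2. Parent-child carrier relation.** Assumptions: Hardy-Weinberg proportions, random mating, carrier coding, risk-allele frequency p of 0.1 to 0.3 (not in the document), and q = 1 − p.

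- P(child non-carrier) = q².
- P(parent carrier and child non-carrier) = 2pq × ½ × q = pq².
- P(parent carrier | child non-carrier) = p.
- P(parent carrier | child carrier) = (1 − q² − pq²)/(1 − q²).
- The difference simplifies to q/(1 + q).

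At p = 0.2: 0.128/0.64 = 0.20 and 0.232/0.36 = 0.644; difference 0.444.

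| p | Trained parent carrier, given carrier child | Given non-carrier child | Difference |
|---|---|---|---|
| 0.1 | 0.57 | 0.10 | 0.474 |
| 0.2 | 0.644 | 0.20 | 0.444 |
| 0.3 | 0.71 | 0.30 | 0.412 |

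With no child susceptibility, 41 to 47% of the parent-driven difference in child effect therefore appears as condition × child genotype when children are pooled. The share is lower in a multilevel model and higher with twin aggregates.

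**3. Size of the parent-driven difference on the child scale.** The 0.47 is an effect on parenting, so it must be multiplied by the parenting-to-child path b. No value is given; 0.2 to 0.5 SD per SD is assumed, with 0.3 as the central value.

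- Parental moderation of 0.47 SD: 0.47 × 0.3 = 0.14 SD on the child.
- Only carrier parents respond, with an average effect of 0.47 and p = 0.2: 0.47/0.36 = 1.31 SD in carriers, and 1.31 × 0.3 = 0.39 SD on the child.

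**4. Simulation.** 225 families, 90 treated, residual twin ICC 0.4, 50% monozygotic, no child moderation, p = 0.2, nominal level 5%. All of these except the family numbers and level are assumptions.

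| Child-scale difference | Model | Spurious child term | Rejection | With parent marker and condition × parent marker |
|---|---|---|---|---|
| 0.14 SD | Multilevel | 0.06 SD | 5.5% | not tabulated |
| 0.39 SD | Multilevel | 0.145 SD | 9.8% | 0.005 SD, 5.5% |
| 0.39 SD | Twin aggregate | 0.201 SD | 12.6% | 0.004 SD, 5.7% |

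With only carrier parents responding, over p = 0.1 to 0.3 and b = 0.2 to 0.5, the spurious term is 0.06 to 0.46 SD with rejection 5.5 to 32% (multilevel), and 0.09 to 0.67 SD with rejection 6 to 43% (aggregate). The upper ends need p = 0.1 and b = 0.5, that is 0.47/0.19 × 0.5 = 1.24 SD on the child. The adjusted term stays between −0.016 and 0.010 SD throughout.

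**5. Sample size.** With 5,000 families (pooled model, p = 0.2, b = 0.3) the spurious term is 0.178 SD and is rejected 92% of the time. The bias does not shrink with N.

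**6. The literal term.** If parenting under Statistical analyses means observed parenting, parenting × child carrier is about 0 in the same setting (at most 0.04 SD with parenting measured at reliability 0.7).

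**The case against.** **The written term is not condition × child marker.** Read as observed parenting, it does not produce this artefact under linearity. That stands. But such a term is not the randomised contrast that aim 4 and the all-aims intention-to-treat statement describe, so the sections disagree whichever was meant.

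**Aim 3 alone is not enough.** The aim 2 path is also needed. That stands; the trial hypothesises both.

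**The size is easily overstated.** A reader might put 0.47 SD directly on the child outcome and infer a gross excess of false positives. The document gives 0.47 for parental sensitivity, and once it is passed through a plausible path the excess is small. Nor does the document support saying that a positive aim 4 result would be just as likely to come from the parent as from the child. The models fail to separate the two, but their relative weight is unknown. For temperament no parent-child correlation is given, so no figure can be attached.

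**The document foresees sibling comparison.** The VIPP-Twins section and Strengths and limitations both mention testing within families, which holds the trained parent fixed. It is not written into the moderation model, however, and the option of aggregate twin scores would remove it.

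**Strengths and limitations is hedged.** It says that randomisation reduces gene-environment correlation, so it should not be read as claiming full removal. The statement in the Background is the unqualified one.

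**Aim 4 is exploratory, and adjustment terms may be left to an analysis plan.** The first part lowers the weight of the point. The second does not remove it, because the article does state which markers enter which models and rests their interpretation on randomisation.

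**Conclusion.** The point holds for aim 4 as a condition-based question. If parental genotype moderates the effect on parenting and parenting carries the effect to the child, the child interaction takes up 41 to 47% of the parent-driven difference when children are pooled, and randomisation does not protect against this. The bias persists at any sample size. In this trial the practical inflation is modest: about 5 to 13% against 5% for child-scale differences of 0.14 to 0.39 SD, and higher only if parental moderation or the path is large. The direction follows from inheritance and the trial's own hypotheses. The magnitudes rest on assumed allele frequency, path size, twin ICC and monozygotic share. It is worth correcting because aim 4 carries part of the trial's theoretical claim and the remedy is cheap, but it does not touch the primary or secondary aims.

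**What to change.** 1. Reconcile the parenting × child marker term under Statistical analyses with the condition-based aim 4 in Aims and hypotheses and the all-aims intention-to-treat statement.
2. In the aim 4 models, fit condition × child marker together with the primary parent's corresponding marker and condition × that marker, each with time as in the main model. Base the exploratory child-susceptibility conclusion on the child term of this joint model. Use the same structure for temperament.
3. Report the within-pair contrast in marker-discordant dizygotic twins as supportive only. About 8 to 16% of pairs would be discordant, that is 18 to 36 of 225 families, of which roughly 7 to 14 are treated.
4. Qualify the statement under Differential intervention effects: randomisation makes condition independent of genotype, but does not separate the child's genotype from the parent's.

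Cost: wording and a few model terms, since parental DNA and temperament questionnaires are already planned. The standard error of the child interaction rises by about 10% (simulated 0.176 against 0.160, and 0.248 against 0.226), so power for aim 4 falls somewhat.

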## Methods/design

### Study design

The L-CID preschooler project is a 4-year randomized controlled trial. Participants are families with twins living in the western region of the Netherlands. The study consists of four assessments. Each assessment consists of a home or laboratory visit and several ambulatory assessments that are carried out by the parents at home. After two baseline assessments in year 1 and year 2, a random 40 % of the sample will receive an intervention aimed at enhancing parental sensitivity and sensitive discipline strategies of the primary caregiver, the VIPP-SD [19]. The first post-test assessment will be carried out one month after the intervention and there will be a long term follow-up two years after the intervention. This protocol paper adheres to the SPIRIT guidelines (see Additional file 1).

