### Statistical analyses

Initial data analysis with data inspection steps will be carried out after the research plan and data collection have been finished but before formal statistical analyses are conducted [42]. We will use double data entry for approximately 20 % of the cases and apply range checks for data values, to promote data quality. It will be tested whether missing data are completely at random, at random, or not at random [43], and multiple imputation procedures will be followed to impute missing data. Data transformation will be applied when necessary to approach normal distribution of data points [44]. To avoid any inflation of statistical tests, we are not planning to examine any interim data-sets.

The overall aim of the study is to estimate the effect of the VIPP-Twins. For all aims, the effect of the VIPP-Twins compared to the control condition will be analyzed using intent to treat analyses. For the primary aim, we propose a repeated measures model to estimate the intervention effect on parental sensitivity and sensitive discipline with experimental condition as between subjects factor and assessment time-point as within subjects factor. The regression coefficient of the interaction between condition and time-point estimates differential changes between the intervention and control groups in parental sensitivity and sensitive discipline over time.

Our secondary aim is to examine the effect of the intervention on children’s levels of behavioral control and social competence. In the current study design, twins are nested within families. Depending on the intraclass correlation (ICC) we will use a multilevel approach with three levels (time-point, child, family) or a repeated measures ANOVA with aggregate scores for the twins within families for analyses with child outcomes. Behavioral control and social competence are included in the analyses using aggregated scores across the different measures.

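### The aim 3 moderation term is named as condition × parental marker without time-point; read literally, it averages in two pre-randomisation waves and halves the mean moderated effect

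*Protocol article*

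**What the plan says.** All the analysis text is in the protocol article, Statistical analyses.

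- **Aim 1 model.** It is a repeated-measures model "with experimental condition as between subjects factor and assessment time-point as within subjects factor". The article says which coefficient carries the intervention effect: "The regression coefficient of the interaction between condition and time-point estimates differential changes between the intervention and control groups".
- **Aims 3 and 4.** Moderation of the intervention effect is examined as follows: "we will include an additional interaction term in the models of aims 1 and 2". For aim 3 the term is then named: "For parenting outcomes, we will include the interaction between condition and parental susceptibility markers (genotype and reactive temperament". Time-point is not part of it, and no other sentence gives a term with condition, time-point and marker together.
- **Design.** Study design states: "The study consists of four assessments". The intervention follows the first two of them ("After two baseline assessments in year 1 and year 2"); the other two are one month and two years after it. Randomization fixes the timing of allocation: "Allocation will be performed after the second pretest, right before the start of the intervention". Both pretests therefore precede randomisation.

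**The concern.** If the intervention effect is condition × time-point, then moderation of that effect by a parental marker is condition × time-point × marker. The two-way term the article names is a different quantity: the marker-related difference between arms, averaged over every assessment in the model. At the two pretests the expected value of that difference is zero, because nobody has yet been allocated. Averaging them in pulls the estimate toward zero. It also admits whatever arm-by-marker imbalance arose by chance at baseline, where a change contrast would subtract it.

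Aim 3 is the parental part of what the Abstract and Discussion present as an experimental test of differential susceptibility theory. A diluted test could return a null result that would be read as evidence against the theory. Leaving open which term is tested would also allow the two-way or the three-way result to be chosen after the data are seen.

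**Working it through.** **The plan's own figures.** Sample size and power gives more than 90% for aim 1, with d = 0.47, α = .05 and 225 families. At 2:3 allocation, 40% of 225 is 90 intervention families, leaving 135 controls. A two-sided comparison of two means (two-sided assumed) gives 93.2%. The within-between F test with f = 0.235 gives at least 99.8% for two to four measures and correlations from 0 to 0.7. The stated figure is reproduced. The figure of more than 80% for aims 3 and 4 cannot be checked, because the article gives no moderator effect, marker frequency or correlation for it.

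**What the two-way term estimates.** Let the moderated effect at the four assessments be (0, 0, δ₁, δ₂). In a balanced repeated-measures model with compound symmetry, condition × marker without time is the equal-weight mean (0 + 0 + δ₁ + δ₂)/4. This is exactly half of the post-intervention mean (δ₁ + δ₂)/2.

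- Sustained effect: (0 + 0 + δ + δ)/4 = 0.50δ.
- Effect halved by two years: (0 + 0 + δ + 0.5δ)/4 = 0.375δ.
- Effect at one month only: (0 + 0 + δ + 0)/4 = 0.25δ.

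A generalised least squares fit gives the same 0.50δ and 0.25δ, with or without a marker × time term. With condition × time-point × marker in the model, the two post-test coefficients recover δ in full and the coefficient between the baselines is 0.

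**How far this depends on the model.**

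- One baseline only in the model, sustained effect: (0 + δ + δ)/3 = 0.67δ.
- AR(1) covariance, correlation 0.3 to 0.7, assumed assessments at about 0, 1, 1.4 and 3.4 years, sustained effect: 0.55δ to 0.56δ.
- Effect growing to 1.5δ by two years: 2.5δ/4 = 0.625 of the one-month effect, still half of the post-test mean of 1.25δ.

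**Loss of information.** With unit variance at each assessment and common correlation ρ, the four-wave mean has variance (1 + 3ρ)/4. The pooled post-test mean minus pretest mean has variance 1 − ρ. For a sustained effect the signals are 0.5δ/√((1 + 3ρ)/4) = δ/√(1 + 3ρ) and δ/√(1 − ρ). The information ratio is (1 + 3ρ)/(1 − ρ):

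- ρ = 0.3: 1.9/0.7 = 2.7
- ρ = 0.5: 2.5/0.5 = 5
- ρ = 0.7: 3.1/0.3 = 10.3

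**Power illustration.** These inputs are assumed, not taken from the article: ρ = 0.5, a binary marker with prevalence 1/3, two-sided 0.05 and a sustained effect. The standard error factor is √[(1/90 + 1/135)/(1/3 × 2/3)] = √(0.01852 × 4.5) = 0.2887. One post-test minus the mean of both pretests has variance 1 + (1 + ρ)/2 − 2ρ = 0.75. Power is Φ(z − 1.96).

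| Test | Standard error | z, power at 0.8 SD | z, power at 0.47 SD |
|---|---|---|---|
| Condition × marker, four-wave mean (estimates δ/2) | 0.2887 × √0.625 = 0.228 | 1.75, 42% | 1.03, 18% |
| Pooled post minus pre | 0.2887 × √0.5 = 0.204 | 3.92, 97.5% | 2.30, 63% |
| One post-test minus mean of both pretests | 0.2887 × √0.75 = 0.250 | 3.20, 89% | 1.88, 47% |

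**The case against.** The strongest reply is that the literal reading is not what the authors mean. The sentence opens by saying that moderation of the intervention effect is to be examined, and the preceding text has just defined that effect as condition × time-point. A repeated-measures ANOVA with condition and marker as between-subject factors would normally report time × condition × marker as well. The paragraph is visibly condensed: the next sentence, on child outcomes, names neither condition nor time-point. On this view the wording is shorthand and the full protocol or analysis plan would spell it out.

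Much of this stands. A reader might infer that the trial will certainly run the diluted test; the article does not establish that. It does, however, go beyond leaving the term open: it names one, the name omits time-point, and nothing elsewhere identifies the three-way term as the test.

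A reader might also infer that every moderated effect shrinks to half or less. That holds for the mean post-intervention effect under equal weighting of four assessments. The article fixes neither the covariance structure nor the number of baselines in the model, and the alternatives above give 0.55δ to 0.67δ for a sustained effect. Nor do the largest power figures carry over to each follow-up separately: 97.5% and 63% belong to the pooled contrast, while a single post-test gives 89% and 47%.

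**Conclusion.** The point holds as a fault of wording with a definite consequence. As written, the aim 3 term does not measure moderation of the effect that the article itself defines. With all four assessments equally weighted, it returns half of the mean post-intervention moderated effect. That result needs only the trial's own schedule and time of randomisation. The information and power losses are illustrative, since correlation, prevalence and effect size are assumed; the direction is the same at every correlation shown.

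This should be fixed before analysis, but it does not threaten the trial's main conclusion. Aim 3 is tertiary, and the primary analysis correctly rests on condition × time-point. A reader might extend the criticism to aim 4, but the child-outcome term there is parenting × child marker. That is a different term raising a separate question, which this point does not settle.

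**What to change.** State in Statistical analyses that aim 3 moderation is tested by condition × time-point × parental marker. Make the pooled post-minus-pre contrast the test, and report the one-month and two-year contrasts alongside it.

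An acceptable alternative is to test condition × marker on post-test scores adjusted for the pretests. This targets the same moderated effect but is a different estimator with its own precision, so the plan should choose one of the two in advance. The aim 4 term needs its own clarification and should not simply be given this wording.

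The cost is one sentence of analysis text, with no change to data collection, sample size or the primary analysis.

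### The interaction stated for aim 4 names parenting, not condition, which contradicts the stated aim and the intention-to-treat rule; the sentence needs correcting

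*Protocol article*

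**What the plan says.** All places are in the Protocol article.

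- **Aims and hypotheses**, aim 4, introduced as more exploratory: "we will examine whether the intervention effect on children’s behavioral control and social competence is moderated by children’s genotype" and/or by reactive temperament.
- **Statistical analyses**, on all aims: the effect of VIPP-Twins against control is analysed by intention to treat.
- **Statistical analyses**, lead-in to the moderator tests: "To examine the moderation of the intervention effect, the third and fourth aim of our study, we will include an additional interaction term". The term extends the models already set up for the first two aims.
- **Statistical analyses**, aim 3: "For parenting outcomes, we will include the interaction between condition and parental susceptibility markers".
- **Statistical analyses**, aim 4, the next sentence: "For child outcomes, we will include an interaction term between parenting and children’s susceptibility markers".
- **Differential intervention effects**, on earlier work: "An important limitation of these studies is their correlational design"; and on this trial: "we break the gene-environment correlation by using a randomized controlled trial with experimental manipulation of the parenting environment".
- **Strengths and limitations**: the reduction in gene-environment correlation is credited to random assignment of families to condition.

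**The concern.** Two adjacent sentences serve the same declared purpose, moderation of the intervention effect, but name different variables. Elsewhere in the article, condition is the randomised arm. Parental sensitivity and sensitive discipline are observed behaviours and form the primary outcome. They are scored for each twin separately, so a score can partly reflect that child's own temperament.

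If an analyst follows the sentence as written, the coefficient says how the association between parenting and child outcome varies with the marker. That is a different quantity from how the effect of being assigned to VIPP-Twins varies with the marker. It also brings back the problem raised in the Background: parent and child share genes, and parenting responds to the child. The abstract and the closing paragraph present the trial as an experimental test of differential susceptibility. For the children, that description depends on a term containing condition. A plan that can be read either way also leaves the choice of term open until the data are seen.

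**Working it through.** **1. The texts side by side.**

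| Element | Aim 3 (parents) | Aim 4 (children) |
|---|---|---|
| Question | moderation of the intervention effect on parenting | moderation of the intervention effect on child outcomes |
| Stated term | condition × parental marker | parenting × child marker |
| First variable randomised? | yes | no, if read literally |
| Compares arms, as the intention-to-treat rule requires? | yes | no, if read literally |

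The aim 4 sentence does not say which parenting measurement is meant. A pre-test score is untouched by the intervention, and a post-test score is one of its outcomes. Neither is randomised. Keeping condition in the model as a main effect does not change what the parenting × marker coefficient estimates.

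**2. The plan's own figures.** Sample size and power gives d = 0.47 (caregiver sensitivity), α = .05 and 225 families. Randomization gives 2:3, that is 90 and 135 families. A simple two-group check for aim 1, two-sided, gives:

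Φ(0.47 × √(90 × 135/225) − 1.96) = Φ(0.47 × 7.348 − 1.96) = Φ(1.494) ≈ 93%

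This agrees with the stated > 90%. The > 80% for aims 3 and 4 cannot be recomputed, because the article gives no interaction size, marker frequency or intraclass correlation. It does not bear on which term is right.

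**3. How much of parenting is randomised (illustration).** With allocation share p = 0.4 and within-arm SD of 1, the share of post-test variance due to condition is p(1−p)d² / [1 + p(1−p)d²].

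- d = 0.47: 0.24 × 0.2209 = 0.0530; 0.0530/1.0530 = 5.0%.
- d = 0.6 (assumed): 0.24 × 0.36 = 0.0864; 0.0864/1.0864 = 8.0%.
- d = 0.3 (assumed): 0.24 × 0.09 = 0.0216; 0.0216/1.0216 = 2.1%.

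The planned models are longitudinal. With d = 0.47 and an assumed pre-post correlation ρ of 0.5 to 0.7, replace the 1 in the denominator as follows:

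- Change scores, 2(1−ρ) = 1.0 to 0.6: 0.0530/1.0530 = 5% to 0.0530/0.6530 = 8%.
- Baseline-adjusted, 1−ρ² = 0.75 to 0.51: 0.0530/0.8030 = 7% to 0.0530/0.5630 = 9%.

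**4. Direction of the error (simulation).** Each setting used 4,000 trials with 90/135 families, one child score per family and no true moderation of the intervention effect. The marker frequency of 0.35 and the confounding strengths are assumptions. Confounding here means an unmeasured family factor that also drives parenting and whose effect on the child differs by marker.

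| Assumed factor × marker strength | Rejections, parenting × marker | Rejections, condition × marker |
|---|---|---|
| 0 | 4.8% | 5.6% |
| 0.2 | 15.5% | 5.8% |
| 0.3 | 30.0% | 5.7% |
| 0.5 | 60.4% | 5.8% |

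The condition term stays near 5% throughout. The parenting term does so only when this confounding is absent.

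**The case against.** The strongest reply is that parenting is shorthand for the parenting intervention. The lead-in speaks of the intervention effect, the term is added to models built to estimate that effect, the intention-to-treat rule covers all aims, and the Background describes the trial as manipulating the parenting environment. This reading is plausible. A reader might infer that the sponsor has chosen a correlational test in place of the randomised one; the article does not establish that. What stands is that the sentence, next to one that says condition, does not state the test the aim requires.

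A second reply is that parenting × child marker has a legitimate use. Aim 2 expects child effects to arise through improved parenting, so the term could be the second path of a moderated-mediation model. That is fair, but it cannot be the only test of aim 4.

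Third, the variance share is not a measure of bias. The d of 0.47 concerns sensitivity only and not discipline. The non-randomised remainder includes measurement error, which weakens the term and is not gene-environment confounding. The simulated rejection rates depend on assumed strengths. All of this stands, so the figures show direction and rough scale only.

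Fourth, aim 4 is labelled more exploratory. This limits the weight of the point.

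**Conclusion.** The contradiction is real and lies in the text: the term stated for child outcomes does not match aim 4 or the intention-to-treat rule, and no condition × child marker term is given. Taken literally, it estimates a different, non-randomised quantity. About 5% of unadjusted post-test parenting variance comes from randomisation at d = 0.47, and about 8% at an assumed d = 0.6. How much bias follows cannot be known from the article.

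This should be fixed, but it does not threaten the main results. The primary aim, the secondary aim and the parental moderation test are unaffected. It would also go too far to conclude that the trial cannot provide an experimental test of differential susceptibility in children. The randomised design supports such a test, and the article separately plans to compare intervention effects between co-twins. Only the sentence specifying the aim 4 term falls short.

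**What to change.** In Statistical analyses, replace the aim 4 sentence with wording such as: *For child outcomes, the test of moderation is the condition × time-point × child susceptibility marker interaction, with all lower-order terms, added to the aim 2 model.*

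The choice between the three-level model and the twin-aggregate ANOVA can stay dependent on the intraclass correlation, as planned. Where co-twins differ on the marker, however, the aim 4 analysis should be at child level, because an aggregate score cannot carry a within-pair difference in the marker.

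If parenting × child marker is still wanted, list it separately and label it as a non-randomised or moderated-mediation analysis.

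The cost is a sentence or two of analysis text and a notice of the modification through the channels the article already names. No new data, visits or participants are needed. The change should be recorded before the aim 4 data are analysed.
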